### Treatment

Eligible patients will be randomly assigned to either the intervention group or the control group. The intervention group will receive QHF for 10 days, and the control group will receive a QHF placebo. QHF is a Chinese herbal compound medicine. The composition of one dose of QHF is provided in the Supplementary material. The main ingredients of QHF placebo include caramel, picrin and burnt grain buds. In this study, concentrated Chinese herbal medicine granules will be used to replicate the traditional method of preparing herbal tonics. All QHF and placebo granules will be produced and packed by New Green Pharmaceutical Co., Ltd., Sichuan, People's Republic of China, with identical color, smell, and weight.

To ensure batch-to-batch consistency, all raw herbs used in QHF are authenticated and comply with the quality standards specified in the Chinese Pharmacopoeia (2020 edition). The manufacturing process is conducted under good manufacturing practice (GMP) conditions by New Green Pharmaceutical Co., Ltd. (Sichuan, China). A certificate of analysis is issued for each production batch.

Chemical fingerprinting of QHF has been established using high-performance liquid chromatography (HPLC). Four representative batches were analyzed, and 18 common peaks were identified in the fingerprint. The similarity between batches was calculated using the Chromatographic Fingerprint Similarity Evaluation Software for traditional Chinese medicine (2012 Edition), and all batches showed a similarity of ≥0.90 compared to the reference fingerprint. Key peaks corresponding to marker compounds such as geniposide, salvianolic acid B, and rhein have been annotated. Detailed fingerprinting data, including chromatograms and similarity results, are provided in the Supplementary material.

**Figure 2 F2:**
[figure not shown]
The flowchart of the QUIET trial. AIS, acute ischemic stroke; BI, Barthel Index; END, early neurological deterioration; MRI, magnetic resonance imaging; mRS, Modified Rankin Scale; NIHSS, National Institutes of Health Stroke Scale; QHF, Qingre Huatan Formula; TCM, traditional Chinese medicine.

### Efficacy outcomes

The primary outcome is the proportion of END within 7 days of stroke onset, defined as an NIHSS score increase of ≥2 points compared with baseline. Secondary outcomes are as follows: (1) change in neurological deficit from baseline to 10 days after randomization; (2) the proportion of patients achieving a good functional outcome, defined as a modified Rankin Scale (mRS) score ≤ 2 on day 30 and 90; (3) activities of daily living measured by Barthel Index (BI) on day 30 and 90.

### Exploratory outcomes

#### Biological outcomes

We will compare between-group changes in intercellular adhesion molecule-1 (ICAM-1), interleukin-6 (IL-6), tumor necrosis factor-α (TNF-α), matrix metalloproteinase-9 (MMP-9) and serum neurofilament light chain (sNfL) levels from baseline to 10 days after randomization. In addition, intestinal microbiota will be profiled by metagenomic sequencing of stool specimens collected at baseline and 10 days after randomization.

#### Neuroimaging outcomes

Infarct volume and the extent of cerebral edema will be quantified using DWI and FLAIR sequences on MRI obtained at baseline and 10 days after randomization.

#### Safety outcomes

Safety will be monitored continuously throughout the trial, capturing all adverse events (AEs), treatment-emergent adverse events (TEAEs), SAEs, and clinically relevant changes in vital signs, physical examination, ECG, and standard laboratory parameters.

An adverse event (AE) is defined as any untoward medical occurrence that emerges or worsens during the study period, from informed consent through final follow-up. AEs will be graded according to the common terminology criteria for adverse events (CTCAE) Version 5.0 as mild (grade 1), moderate (grade 2), severe (grade 3), life-threatening (grade 4), or fatal (grade 5). treatment-emergent adverse events (TEAEs) are AEs that occur or worsen following the first dose of study medication.

Serious adverse events (SAEs) are defined as any AE that,s regardless of dose or causality: (1) results in death; (2) is life-threatening; (3) requires inpatient hospitalization or prolongation of existing hospitalization; (4) results in persistent or significant disability or incapacity; (5) is a congenital anomaly or birth defect; or (6) requires intervention to prevent permanent impairment or damage.

At each study visit, participants will be systematically questioned about any AEs using non-leading questions. All AEs, regardless of severity or causality, will be recorded in CRFs with detailed information including onset date, duration, severity, relationship to study drug, actions taken, and outcome. The relationship between the AE and the study drug will be assessed by the site investigator using a five-category scale: definitely related, probably related, possibly related, probably unrelated, or definitely unrelated. All AEs will be managed according to standard clinical practice, with appropriate treatment provided as necessary.

All SAEs must be reported to the principal investigator within 24 h of awareness. The principal investigator will then report the SAEs to the institutional review board (IRB) and the DSMB within the required timeframe (typically within 7 calendar days for fatal or life-threatening events, and within 15 calendar days for other SAEs). All SAEs will be followed until resolution or stabilization.

The overall schedule of trial-related activities and data collection is presented in Table 2.

**Table 2 T2:** Schedule of the study process.

Time point	Treatment period					Follow-up period	
	Baseline (Day 1)	Day 3	Day 5	Day 7	Day 10 or discharge	Day 30	Day 90
Eligibility screening	×						
Informed consent	×						
Demographics	×						
Medical history	×						
Vital signs	×				×		
Physical examination	×				×		
Neurological evaluation	×	×	×	×	×		
CT/MRI	×				×		
ECG	×				×		
Laboratory examination	×				×		
Allocation	×						
TCM syndromes	×			×	×		
NIHSS	×	×	×	×	×		
mRS						×	×
BI						×	×
Serum sample	×				×		
Stool sample	×				×		
Concomitant medications					×	×	×
Complications	×	×		×	×		
AEs and SAEs	×	×	×	×	×	×	×

AE, adverse event; BI, Barthel Index; CT, computed tomography scan; ECG, electrocardiogram; MRI, magnetic resonance imaging; mRS, Modified Rankin Scale; NIHSS, National Institutes of Health Stroke Scale; SAE, serious adverse event; TCM, traditional Chinese medicine.

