## Introduction

Stroke is a major global health threat, imposing a substantial burden on individuals and public health systems (1, 2). Ischemic stroke constitutes roughly two-thirds of all new stroke events worldwide (3). Acute ischemic stroke (AIS) is marked by abrupt neurological deficit onset and rapid clinical progression, often culminating in severe disability. Despite guideline-based usual care, however, 5%−40% of patients develop early neurological deterioration (END) within hours or days of symptom onset (4), which is associated with poor clinical outcomes and increased mortality (4–7).

END is one of the most significant challenges in AIS management. Currently, its clinical handling faces three core dilemmas: First, its pathogenesis involves multiple pathophysiological pathways that are intrinsically complex and accompanied by numerous risk factors (8). Second, validated early prediction tools are lacking, impeding rapid identification of high-risk END patients shortly after onset and thereby delaying intensified monitoring and individualized intervention. Moreover, current reperfusion, antithrombotic and neuroprotective strategies show limited efficacy specifically targeting END (9). As a result, the development of safe and effective therapies for this condition has become an urgent unmet need in the acute management of ischemic stroke.

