## Methods

### Study design

The Qingre Huatan Formula for the prevention of early neurological deterioration in acute ischemic stroke (QUIET) trial is a randomized, placebo-controlled, double-blind, parallel-group pilot study registered with ClinicalTrials.gov (NCT06857487) prior to patient enrollment. The primary objective of this study is to assess the effectiveness and safety of QHF vs. placebo for AIS patients at high risk of END. We hypothesize that QHF will be superior to placebo at reducing the risk of END within 7 days of stroke onset, defined as a National Institutes of Health Stroke Scale (NIHSS) score increase of ≥2 points. Furthermore, we will explore the neuroimaging, biological indicators and other dimensions of patients suffering from the phlegm-heat syndrome in AIS. This trial protocol was approved by the institutional review board of Dongzhimen Hospital, Beijing University of Chinese Medicine, Beijing, China (No. 2023DZMEC-410-02). The protocol design is based on the Standard Protocol Items: Recommendations for Interventional Trials (SPIRIT) guidelines (15). The SPIRIT checklist is shown in the Supplementary material.

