### Statistical analyses

Statistical analyses will be conducted using three datasets: the full analysis set (FAS), the per-protocol set (PPS), and the safety set (SS). The FAS will include all randomized participants with at least one post-baseline assessment, with missing data imputed using the multiple-imputation method (23). Sensitivity analyses will be conducted using last observation carried forward (LOCF), worst-case, and best-case scenarios to assess the robustness of the primary outcome under different missing data assumptions. The PPS will comprise only those who fully comply with the protocol without major deviations. The SS will include all participants who receive at least one dose of the study drug and undergo at least one safety evaluation. Both efficacy and safety analyses will follow the intention-to-treat principle. Qualitative variables will be summarized using frequencies and percentages, while quantitative variables will be presented as means ± standard deviations for normally distributed data or medians with interquartile ranges for non-normally distributed data.

For the primary efficacy outcome, the incidence of END will be compared between groups using the chi-square or Fisher exact test, as appropriate. Risk differences and 95% confidence intervals will be reported. Secondary efficacy outcomes such as BI scores, changes in NIHSS scores, and relevant biomarkers will also be compared between groups using Student's *t*-test or the Wilcoxon rank-sum test, with mean differences and 95% confidence intervals reported where applicable. Additionally, the proportion of patients with a mRS grade ≤ 2 and the incidence of AEs will be compared using the chi-square test or Fisher exact test, as appropriate.

Prespecified subgroup analyses for the primary outcome will be performed according to the following baseline characteristics: age (>65 years vs. ≤ 65 years); sex (female vs. male); symptom onset to randomization time ( ≤ 24 h vs. >24 h); medical history (hypertension, diabetes mellitus, coronary heart disease, stroke, and hypercholesterolemia); smoking history; Trial of Org 10172 in acute stroke treatment (TOAST) classification; presence of large artery stenosis; stroke severity based on baseline NIHSS score ( ≤ 5 vs. >5); and severity of phlegm-heat syndrome.

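### As defined, adverse events include early neurological deterioration, so the between-arm comparison of AE incidence can mix the efficacy effect with other harms; a with/without split should be added

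*Protocol article*

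**What the plan says.** Three sections of the protocol article meet on this point.

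- **Efficacy outcomes.** "The primary outcome is the proportion of END within 7 days of stroke onset, defined as an NIHSS score increase of ≥2 points". The reference point is the baseline score. Study design gives the expected direction: "We hypothesize that QHF will be superior to placebo at reducing the risk of END within 7 days of stroke onset".
- **Safety outcomes.** An AE is "any untoward medical occurrence that emerges or worsens during the study period, from informed consent through final follow-up". The recording rule is equally wide: "All AEs, regardless of severity or causality, will be recorded in CRFs". One of the SAE criteria is an event that "results in persistent or significant disability or incapacity"; death, threat to life and prolonged hospitalization are others. The section does not exempt END, stroke progression or efficacy endpoints.
- **Statistical analyses.** On safety, "the incidence of AEs will be compared using the chi-square test or Fisher exact test, as appropriate". No AE comparison that sets END aside is described.

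Study design places safety beside effectiveness in the primary objective, and Sample size calculation names safety among the main purposes of the pilot.

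**The concern.** A rise of at least 2 NIHSS points after consent is an untoward occurrence that worsens during the study, so it fits the AE definition. If it prolongs the hospital stay or leaves significant disability, it also fits the SAE definition. A patient with END then counts once in the primary efficacy outcome and again in the AE total.

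The two counts should move in opposite directions if QHF both works and has side effects. Fewer END events lower the AE percentage on QHF, while drug-related events raise it. A single pooled percentage cannot separate the two. It could understate an excess of other AEs, or make QHF look safer purely because it prevents END. If QHF has no effect on END, the END events still dilute any difference in the rest.

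Classification has further consequences. Treatment stops the study drug when an SAE occurs. Randomization, allocation, and blinding allows emergency unblinding for SAEs under stated conditions and removes unblinded patients from per-protocol analyses. Whether END is an SAE therefore bears on those rules and on the per-protocol set.

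**Working it through.** The article states no AE rate, planning rate for END, effect size or power, so there is no figure to reproduce. The check shows how far the pooled percentage could move.

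**Inputs from the article.** The Introduction says that "5%−40% of patients develop early neurological deterioration (END) within hours or days of symptom onset", despite usual care. Patient selection restricts entry to patients at high risk of END. There are 36 patients per arm (Sample size calculation), and tests are two-sided at 0.05 (Statistical analyses).

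**Assumptions not in the article.** Every END is counted as an AE. END and other AEs are independent. Other AEs occur in 20% on placebo and 32% on QHF, a true excess of 12 points. QHF either halves END or leaves it unchanged.

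**Formula.** In each arm, P(any AE) = 1 - (1 - END) × (1 - other AE). If END is equal in both arms, the difference reduces to (1 - END) × 12 points.

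| Placebo END | Any AE, placebo | Any AE, QHF (END halved) | Difference, END halved | Difference, END unchanged |
|---|---|---|---|---|
| 5% | 1 - 0.95 × 0.80 = 24.0% | 1 - 0.975 × 0.68 = 33.7% | +9.7 | +11.4 |
| 10% | 1 - 0.90 × 0.80 = 28.0% | 1 - 0.95 × 0.68 = 35.4% | +7.4 | +10.8 |
| 20% | 1 - 0.80 × 0.80 = 36.0% | 1 - 0.90 × 0.68 = 38.8% | +2.8 | +9.6 |
| 30% | 1 - 0.70 × 0.80 = 44.0% | 1 - 0.85 × 0.68 = 42.2% | -1.8 | +8.4 |
| 40% | 1 - 0.60 × 0.80 = 52.0% | 1 - 0.80 × 0.68 = 45.6% | -6.4 | +7.2 |

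With END halved, the difference is 0.12 - 0.46 × END. It crosses zero at 0.12 / 0.46, a placebo END rate of about 26%.

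**No toxicity.** With other AEs at 20% in both arms and END falling from 40% to 20%, any-AE incidence is 1 - 0.60 × 0.80 = 52% on placebo and 1 - 0.80 × 0.80 = 36% on QHF. The whole 16-point gap is the efficacy effect.

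**Dependence.** At 30% placebo END, if END and other AEs never fall in the same patient, the rates add: 50% against 47%, or -3 points. If they overlap completely, the larger rate applies: 30% against 32%, or +2 points. Either way, most of the 12 points is lost at that END rate.

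**Power.** For other AEs of 20% against 40% and 36 per arm, exact enumeration of Fisher's test gives a 37% chance of a significant excess on QHF when END is kept apart. With END pooled in and halved by QHF, this becomes 27% at 5% placebo END and 8% at 20%.

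**The case against.** The strongest reply is that the overlap is inferred. END is never named as an AE. The definition is generic, and handling of endpoint events is often left to the full protocol, form instructions or analysis plan, none of which is available here. The schedule of the study process (Table 2) lists NIHSS and complications separately from AEs and SAEs, and Follow up procedures lists stroke recurrence and new vascular events as their own items. This stands as a limit: double counting is possible under the text, not established. It does not remove the point, because the article itself gives both an all-inclusive definition and the comparison built on it.

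A reader might infer that toxicity of QHF would go unseen. The documents do not support that. Each AE carries a severity grade and a five-category causality rating. Laboratory, ECG and vital-sign changes are captured as well, and the safety board reviews unblinded safety data. END itself is reported by arm with a risk difference, so its contribution can be judged.

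A reader might also infer that END is one of the commonest AEs, or that the AE comparison fails at any END rate. No AE rate is given, and at 5% placebo END most of the excess survives. High-risk enrolment makes higher rates plausible, but none is stated.

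Finally, it is tempting to make the count without END the safety measure. The Discussion lists hemorrhagic transformation, cerebral edema and seizures among the causes of END, so that choice could remove treatment-caused harm. This objection stands in full and shapes the remedy.

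**Conclusion.** The point holds in a limited form. On the stated wording, the primary efficacy event falls inside the AE definition, and the planned comparison of AE incidence can mix benefit with harm. The distortion ranges from slight to a change of sign: a 12-point excess of other AEs shows as +9.7 points at 5% placebo END, +7.4 at 10% and -1.8 at 30% if QHF halves END, and as 11.4 to 8.4 points over 5% to 30% if it does not affect END. These figures rest on assumed other-AE rates, an assumed halving of END, independence, and every END being recorded as an AE.

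Only the pooled AE incidence, and any SAE incidence on the same definition, is affected. The consequence is also bounded by the trial's size: even with END kept apart, Fisher's test at 36 per arm has only 37% power for 20% against 40% other AEs and 29% for 10% against 25%. This is an inexpensive improvement to the safety reporting. It does not show that harm would be missed. If the full protocol already says how END is classified, a sentence to that effect settles that part.

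**What to change.** 1. In Safety outcomes, state whether END is recorded as an AE and, where it meets a criterion, as an SAE.
2. In Statistical analyses, keep all-cause AE and SAE incidence as the reported between-arm comparison. Add beside it the same comparison excluding worsening that meets the END definition.
3. Tabulate END-related AEs and SAEs separately by arm and by cause, so that END due to hemorrhage, edema or seizure stays visible as possible harm.
4. Give the safety board the same split.
5. Reconcile the classification of END with the SAE-based discontinuation text in Treatment and the SAE-based unblinding text in Randomization, allocation, and blinding. Which clinical rule should apply is for the investigators to decide.

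The cost is a sentence or so in each section concerned, one flag on the AE form and one extra table. The flag draws on the NIHSS scores and AE details already collected. Recording and reporting of events need not be reduced. The drawback is two AE totals to explain. The split should be fixed before the blind is broken.

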**Methods:**

The Qingre Huatan Formula for the Prevention of Early Neurological Deterioration in Acute Ischemic Stroke (QUIET) trial is a randomized, placebo-controlled, double-blind, parallel-group pilot study. Seventy-two eligible patients with AIS within 48 h of symptom onset will be randomly (1:1) assigned to receive either QHF or placebo treatment for 10 days and will subsequently be followed up to 90-days. The primary outcome is the proportion of END within 7 days of stroke onset, defined as a National Institutes of Health Stroke Scale (NIHSS) score increase of ≥2 points. Secondary outcomes mainly include the change in NIHSS score from baseline to 10 days after randomization, and the proportion of patients achieving a good functional outcome (modified Rankin Scale score ≤ 2).

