### Follow up procedures

All follow-up assessments will be performed by independent interviewers trained in neurology who are certified according to a standard operating procedure (SOP) and remain fully blinded to treatment allocation throughout the trial. Structured telephone interviews will be conducted standardized CRF forms at 30 and 90 days after symptom onset. The CRFs include mRS and BI scores, stroke recurrence, new-onset vascular events, medication use, and rehabilitation services received during the follow-up period. All interviews will be recorded and saved.

NIHSS assessments will be performed by certified neurologists or neurology residents who have completed standardized NIHSS training. All assessors will be blinded to treatment allocation. Prior to study initiation, assessors will be required to achieve ≥90% agreement with expert consensus scores across 10 validation cases. Throughout the trial, 10% of assessments will be randomly audited by an independent expert, and periodic refresher training will be conducted to maintain inter-rater reliability.

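### The one between-arm safety comparison named counts AEs from consent to Day 90 for a 10-day treatment, so harm confined to the dosing period is diluted

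*Protocol article*

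**What the plan says.** All references are to the protocol article.

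- **AE window.** Safety outcomes defines an AE as "any untoward medical occurrence that emerges or worsens during the study period, from informed consent through final follow-up". Table 2 schedules AE and SAE recording at baseline, Days 3, 5, 7 and 10, and Days 30 and 90.
- **TEAEs.** The same section lists the safety data as "capturing all adverse events (AEs), treatment-emergent adverse events (TEAEs), SAEs" and other items. It says that TEAEs "are AEs that occur or worsen following the first dose of study medication". A start is given, but no end.
- **Comparison.** Statistical analyses says that "the incidence of AEs will be compared using the chi-square test or Fisher exact test, as appropriate". It states no counting window and does not mention TEAEs. The safety set in that section selects patients by dosing and safety evaluation; it does not restrict event dates.
- **Exposure and follow-up.** Under Treatment, "The intervention group will receive QHF for 10 days, and the control group will receive a QHF placebo". Follow-up procedures places the last two contacts "at 30 and 90 days after symptom onset".
- **Data recorded.** Safety outcomes records onset date and relationship to study drug for every AE.

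**The concern.** Safety is part of the primary objective (Study design) and of the pilot's declared purpose (Sample size calculation). Chi-square and Fisher exact tests compare proportions, so the natural reading of the planned test is the share of patients with at least one AE, as AEs are defined. Most of that window lies after the last dose. A patient with an unrelated event on Day 60 counts the same as one with an event on Day 4, and a patient who has already had a background event cannot add to any excess. If QHF raises AE risk only while it is taken, the named comparison understates that excess.

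Moving to TEAEs as now defined would not solve this. It would remove events before the first dose, but an event on Day 85 would still count as treatment-emergent.

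**Working it through.** The article gives no AE rate, safety effect or safety power, so there is no figure to reproduce. All rates below are assumptions.

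**Inputs from the article:** 10 days of treatment; last contact at 90 days from symptom onset; enrolment within 48 h of onset; 36 patients per arm; two-sided 0.05.

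**1. Off-drug time.** 90 − 10 = 80 days, or 90 − 10 − 2 = 78 days if dosing starts 48 h after onset. As a share of 90 days this is 78/90 = 87% to 80/90 = 89%.

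**2. General result.** Let p_C and p_T be the on-treatment AE risks (placebo, QHF). Let b be the risk of an AE outside treatment, equal in both arms and independent of the on-treatment risk. The risk over the whole span is 1 − (1 − p)(1 − b), so the difference over the whole span is (p_T − p_C)(1 − b). The shrinkage factor does not depend on p_C or p_T.

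**3. Size, with 60% of placebo patients having an AE by Day 90 and the hazard doubled on drug.** The total background hazard is H = −ln(0.4) = 0.916. A share s of it falls in the first 10 days. On-treatment risks are 1 − exp(−sH) and 1 − exp(−2sH). Day-90 risks are 0.60 and 1 − exp(−(1 + s)H).

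| Share s in first 10 days | On treatment | Difference, RR | To Day 90 | Difference, RR |
|---|---|---|---|---|
| 1/9 (constant hazard) | 9.7% vs 18.4% | +8.7 points, 1.90 | 60.0% vs 63.9% | +3.9 points, 1.06 |
| 1/2 | 36.8% vs 60.0% | +23.2 points, 1.63 | 60.0% vs 74.7% | +14.7 points, 1.25 |
| 0.7 | 47.3% vs 72.3% | +24.9 points, 1.53 | 60.0% vs 78.9% | +18.9 points, 1.32 |

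Check against step 2: in the constant-hazard row b = 0.557, and 8.7 × 0.443 = 3.9; in the second row b = 0.368, and 23.2 × 0.632 = 14.7.

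Under a constant hazard with a placebo Day-90 risk of 40% or 80%, the RR falls from 1.94 to 1.08 or from 1.84 to 1.04.

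**4. A second illustration, with power at 36 per arm.** Assume on-treatment risks of 20% and 45%.

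| b | Risks compared | Difference | RR | Power, chi-square / Fisher |
|---|---|---|---|---|
| 0 | 20% vs 45% | 25 points | 2.25 | 62% / 54% |
| 0.2 | 36% vs 56% | 20 points | 1.56 | 40% / 30% |
| 0.4 | 52% vs 67% | 15 points | 1.29 | 25% / 17% |
| 0.6 | 68% vs 78% | 10 points | 1.15 | 16% / 10% |

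**5. Pre-dose events.** Table 2 puts consent and allocation both on Day 1. A pre-dose risk of 1% to 5% takes 0.25 to 1.25 points off the 25-point difference (24.75 to 23.75).

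**The case against.** **An article condenses the plan.** The end of a TEAE window and the layout of safety tables are ordinary content for an analysis plan, which is not shown. Onset dates and relatedness are recorded, so nothing blocks an on-treatment analysis. This limits what can be said: it cannot be claimed that no such analysis is planned. It does not dispose of the point, because the article names the compared quantity and defines both terms, and the TEAE definition it gives would leave the off-drug dilution in place.

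**AEs are likely to be front-loaded.** Patients are enrolled within 48 h of stroke. AE questioning is dense to Day 10; after that there are only two telephone contacts. Vital signs, examination, ECG and laboratory tests are scheduled only at baseline and Day 10. A constant hazard fits this poorly, so the fall to RR 1.06 is the unfavourable end of the range. This stands. With half the hazard in the first 10 days, more than a third of the difference is still lost (23.2 to 14.7 points); with 70%, about a quarter (24.9 to 18.9).

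**The pilot is too small either way.** In the constant-hazard case, on-treatment power is about 18% (chi-square) or 11% (Fisher), against about 5% or 3.5% to Day 90. With half the hazard early it is about 51% or 40%, against 26% or 19%. This also stands: a non-significant safety result would often follow from size alone. The point estimate and its interval are still shifted by the choice of window.

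**Other safeguards exist.** CTCAE grading, causality assessment, SAE reporting and a DSMB that sees unblinded AE and laboratory data all offer routes to detect harm. They do not change what the planned comparison estimates.

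**Stronger readings.** A reader might infer that any harm of QHF is diluted, that pre-dose events are a material part of the problem, or that following AEs to Day 90 is itself a mistake. The documents support none of these. Delayed or persisting harm needs the Day-90 count, consent and allocation fall on the same day, and long follow-up is sound. The weakness is that the pooled count is the only comparison named.

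**Conclusion.** The point holds for harm confined to the dosing period. The direction and the factor (1 − b) follow from the stated definitions, given an equal and independent off-treatment background risk in both arms. The size cannot be fixed from the documents. Under the 60% assumption with a doubled on-drug hazard, the risk ratio falls from 1.90 to 1.06 if the hazard is constant, and from 1.63 to about 1.25 if half of it falls in the first 10 days; the second is the more plausible shape for acute stroke with this visit schedule. The change should be made, but it does not threaten the trial.

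**What to change.** - **Safety outcomes:** give the TEAE definition an end, namely the end of treatment plus a run-off that the sponsor fixes before unblinding. Choosing the window after unblinding would undermine the comparison.
- **Statistical analyses:** compare the incidence of on-treatment TEAEs between arms, with a risk difference and 95% CI.
- **Keep the Day-90 comparison of AEs and SAEs beside it**, so that delayed harm stays visible.

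**Cost:** wording in two sections and one more safety table. Onset dates are already collected, so no visit, data item or treatment changes. Power for either comparison remains low at 36 per arm, and the report should rely on the interval rather than on the p-value.
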